**Fig. 2 Fig2:**
[figure not shown]
Delayed-start design with beneficial effect of early treatment with levodopa. If a beneficial disease modifying effect of levodopa exists, patients in the early-start group will perform better at the end of the study than patients in the delayed-start group if phase 1 is sufficiently long and if the beneficial disease modifying effect is maintained during phase 2. The small improvement of the delayed-start group at the start of phase 1 and of the early-start group at the start of phase 2 represents the placebo-effect

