Randomisation is performed by a central website based computer program in 1:1 ratio (Fig. 1) and stratified by type of hospital (university medical centre versus non-university medical centre), age (below 65 years or 65 years and older), and symptom duration (shorter than 0.5 year or 0.5 year and longer), using variable permuted blocks. Study personnel, research nurses, neurologists, and patients are blinded to the treatment allocation at all times. ACE Apothecary (ACE Apotheek, Zeewolde, The Netherlands) allocates the randomised patient to a medication number that corresponds with the treatment group and ACE Apothecary is responsible for packaging, labelling and shipment of the study medication during the first 42 weeks of the study. Randomisation data are kept strictly confidential and are accessible only to authorised persons at ACE Pharmaceuticals and ACE Apothecary until the database is unlocked at the end of the study. All data will be entered in a central website based database before the database is unlocked.

Approval of the medical ethical committee of the Academic Medical Center was obtained. The LEAP-study is conducted according to the principles of the Declaration of Helsinki (version 2008). Study monitoring and data management are performed in accordance with the International Conference on Harmonisation - Good Clinical Practice guidelines. This is an investigator-initiated study. None of the funding organisations has influence on the design or execution of the trial, the analysis of the study data, or the publication of articles concerning the study data.

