### Statistics

Based on the ELLDOPA study, we assume a mean baseline UPDRS score of 28 points with a standard deviation of 13 points and anticipate a mean UPDRS score in the early-start group of 31 points (worsening of 3 points during follow-up) and a mean UPDRS score in the delayed-start group of 35 points (worsening of 7 points) at the final outcome assessment at 80 weeks [3]. Assuming that the common standard deviation is 13, a sample size of 167 in each group will have 80 % power to detect a difference in mean follow-up scores of 4 points, using a two-group *t*-test with a 0.05 two-sided significance level. In the ELLDOPA study, a dropout rate of 22.2 % was reported in the placebo group [3]. After 80 weeks, the ADAGIO-study reported a total dropout rate of 24.4 % in the 1 mg delayed-start group and 19.2 % in the 2 mg delayed-start group. Based on these results, a total withdrawal rate of 25 % was considered realistic [19]: therefore, we plan to include 223 patients per treatment arm, which means 446 patients in total (Fig. 3).

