**Fig. 3 Fig3:**
[figure not shown]
Flow chart LEAP-study. Taking into account a withdrawal rate of 25 %, 446 patients need be enrolled to be able to show a minimal clinically relevant difference of four points on the total UPDRS at the end of the study

Data will be analyzed according to the intention-to-treat principle. The main analysis of this trial consists of a comparison between the trial treatment groups of the primary outcome after 80 weeks. First, the follow-up difference of mean UPDRS scores between the treatment arms will be crudely analyzed using a two-group *t*-test. Second, the UPDRS follow-up scores will be further investigated using analysis of covariance (ANCOVA), taking into account patients’ UPDRS baseline values. To account for the repeated measures within patients, a random effects model will be used.

With regard to the comparisons of the secondary outcome progression of symptoms during phases 1 and 2 we planned two separate analyses using a random effects model to account for the repeated measures within patients (Fig. 2). For phase 1, we will use the measurements of Visit 2 (4 weeks), Visit 3 (22 weeks) and Visit 4 (40 weeks) to estimate the difference in slopes between the two treatment groups. A more progressive course (steeper upward slope) in the placebo group during phase 1 can reflect disease-modifying effects of levodopa. This will be further explored by examining the slopes of phase 2. Equal steepness of the slope during phase 2 indicates that the (assumed) effect found in phase 1 is a true disease-modifying effect. Therefore, we will use measurements of Visit 5 (44 weeks), Visit 6 (56 weeks), Visit 7 (68 weeks), and Visit 8 (80 weeks) to test equality of progression in phase 2 with a non-inferiority test on the difference between the slopes of the two treatment arms using a non-inferiority margin of 0.055 UPDRS points difference in increase per week (Fig. 2). The slopes of the phases 1 and 2 will be analysed by both an intention-to-treat and a per-protocol approach (see below for further explanation).

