As pointed out earlier, the main outcome in this study will be the comparison between treatment arms on UPDRS scores after the total study period of 80 weeks, since this outcome relates to clinical practice. A difference of four points on the total UPDRS is considered to be clinically relevant [20]. The comparisons of slopes in the secondary analyses serve only to differentiate between the different types of treatment effects (direct symptomatic vs disease modifying). Here we pre-specify the possible inference made on these secondary analyses:if a faster progression is found in the placebo group during phase 1 and the non-inferiority assumption assuming equal progression is met in phase 2, this will be indicative of a true disease-modifying effect;if a faster progression is found in the placebo group during phase 1, but non-inferiority of slopes during phase 2 is not demonstrated, then the results are indicative of only direct symptomatic effects.

With regard to the comparisons of the other secondary outcomes (disability, number of patients that need additional medication for PD, cognitive impairment, mood, quality of life, ability to (maintain) work, use of (informal) care, caregiver burden, levodopa-induced response fluctuations, and side effects), we will use the appropriate parametric and nonparametric statistics. Cost-effectiveness and cost-utility analyses will be performed from a societal perspective with the costs per unit decrease on the UPDRS respectively, the costs per QALY as outcomes. In all analyses statistical uncertainties will be expressed in 95 % confidence intervals.

Subgroup analyses by type of hospital (university medical centre versus non-university medical centre), age and disease duration will be performed. Finally, two additional ‘per protocol’ analyses will be carried, focusing on (a) between-group difference in UPDRS scores at 80 week and the progression of UPDRS scores during phases 1 and 2, and (b) between-group difference in UPDRS scores at 80 weeks and the progression of UPDRS scores during phases 1 and 2 in patients in the highest quartile of scores at baseline. Patients will be excluded from the per protocol analysis if they needed additional PD-medication during the study, if they did not use the correct dose and type of medication (e.g., extended release levodopa formulations), or if they missed either Visits 1, 2, 4, 5 or 8.

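### The rule for concluding disease modification rests on slopes alone and does not require an early-start advantage at week 80

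*Protocol article*

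**What the plan says.** Methods, Statistics sets out two secondary slope analyses: phase 1 from weeks 4, 22 and 40, and phase 2 from weeks 44, 56, 68 and 80. The phase 2 comparison is a non-inferiority test with a margin of 0.055 UPDRS points per week.

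The reading of these analyses is fixed in advance. Given steeper worsening on placebo in phase 1, if "the non-inferiority assumption assuming equal progression is met in phase 2, this will be indicative of a true disease-modifying effect". The description of the phase 2 analysis says the same: "Equal steepness of the slope during phase 2 indicates that the (assumed) effect found in phase 1 is a true disease-modifying effect". Neither sentence mentions the week-80 result.

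Week 80 is the primary outcome, but the article justifies it by its relevance to practice. Telling symptomatic from disease-modifying effects is assigned to the slopes.

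The Fig. 2 caption (Trial design) describes disease modification differently. If such an effect exists, phase 1 is long enough and the effect is maintained in phase 2, then "patients in the early-start group will perform better at the end of the study than patients in the delayed-start group".

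**The concern.** In a delayed-start design, the evidence that separates the two explanations is whether a gap remains once both arms are on active drug. A slope comparison discards level. Parallel phase 2 lines may lie apart, which is disease modification, or on top of each other, which is full catch-up. The rule accepts both.

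The phase 1 condition does not close this hole. Placebo scores can worsen faster than treated scores between weeks 4 and 40 without any change in the disease, for example when the symptomatic benefit increases as untreated severity increases.

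A trial with no benefit at week 80 could then be reported, under its own pre-specified rule, as indicating disease modification. The Discussion says that demonstrating this effect would support starting treatment at diagnosis, so the reading matters even though the analyses are secondary.

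**Working it through.** **The plan's own figure.** Inputs from Statistics: difference 4 points, SD 13, 80% power, two-sided 0.05, 25% withdrawal.

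- Normal approximation: n = 2 × (1.96 + 0.842)² × 13² / 4² ≈ 165.8, so 166 per arm. The exact two-sample t-test gives 166.8, so 167.
- 167 / 0.75 = 222.7, so 223 per arm and 446 in total.

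The stated size is reproduced. It covers only the week-80 comparison. The article states no error rate or power for the slope rule, so there is none to reproduce.

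**A counter-example in means.** Start from the article's baseline mean of 28. Assume untreated worsening of 0.20 points per week and a drug that removes 30% of the current score, fully reversibly.

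| Week | Untreated | Treated | Gap |
|---|---|---|---|
| 4 | 28.8 | 20.16 | 8.64 |
| 40 | 36.0 | 25.2 | 10.8 |
| 80 | (44.0) | 30.8 in both arms | 0 |

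The phase 1 slope difference is (10.8 − 8.64) / 36 = 0.06 per week. The phase 2 slopes are identical and the week-80 difference is 0. Both conditions of the rule hold in truth, with no disease modification.

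**How often the rule would be met, assumption set A.** Residual SD 5, between-patient slope SD 0.15 per week, 167 per arm. Phase 1 is tested at two-sided 0.05. Non-inferiority requires the 95% limit to lie below 0.055.

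- Phase 1: Sxx for weeks 4, 22, 40 is 648. SE = √(0.15² + 25/648) × √(2/167) = 0.0270. P = Φ(0.06/0.0270 − 1.96) = 0.60.
- Phase 2: Sxx for weeks 44, 56, 68, 80 is 720. SE = √(0.15² + 25/720) × √(2/167) = 0.0262. P = Φ(0.055/0.0262 − 1.96) = 0.56.
- Both: 0.602 × 0.556 ≈ 0.335 if the two are independent. It is about 0.39 to 0.40 if each patient's slope deviation carries over from phase 1 to phase 2.
- For a 20-40% effect and worsening of 0.15-0.25 per week, the joint probability is roughly 10-55%.

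**Assumption set B, by simulation.** 3000 trials per scenario, 167 per arm, the protocol's visit weeks, total SD 13 at week 80. Per-patient least-squares slopes stand in for the random effects model. The three columns are residual SD / slope SD.

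| Scenario | 4 / 0.05 | 5 / 0.10 | 6 / 0.10 |
|---|---|---|---|
| Reversible, 25% of severity, 0.2 per week | 70% | 38% | 25% |
| Reversible, 50% of severity, 0.2 per week | 89% | 64% | 50% |
| Reversible, 30% of severity, 0.3 per week | 89% | 63% | 48% |
| Constant, immediate 5-point effect | 3% | 2% | 1% |
| Slow-onset effect, highest of four shapes | 6% | 5% | 3% |
| True 4-point disease-modifying effect | 89% | 65% | 51% |

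In the three severity-proportional scenarios the week-80 test favours early start in only 2-3% of trials.

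**With a week-80 condition added.** The severity-proportional scenarios fall to about 2-2.5%. The true 4-point effect falls to 73%, 58% and 47%.

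**The case against.** **The week-80 context is already there.** It is the primary outcome and the main analysis, and the article says that the slopes serve only to sort types of effect, which suggests there is an effect to sort. Fig. 2 shows the early group ahead at the end, and both the slope analyses and the Discussion point to Fig. 2. On this reading the defect is an unstated link. That is a fair account of the intention, but the text does not say it: the sentence on phase 2 slopes ties the inference to the effect found in phase 1, not to the week-80 result.

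**The rule does screen out simple symptomatic effects.** This stands. A reader might infer that any purely symptomatic drug could pass. A constant effect produces no phase 1 slope difference. With a slow-onset effect, catch-up in the delayed arm usually defeats the non-inferiority test. High pass rates need a benefit that grows between weeks 4 and 40 and is caught up by about week 44. The documents do not say whether levodopa behaves this way.

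**The margin.** A reader might also infer that the margin is too loose to help, because 0.055 × 36 weeks = 1.98 points, about half of the 4-point difference. That does not follow. The confidence limit, not the estimate, must lie below 0.055. With the set A standard error, the observed slope difference must be below 0.055 − 1.96 × 0.0262 ≈ 0.004 per week, about 0.13 points over 36 weeks. A true difference at the margin would pass only about 2.5% of the time.

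**Secondary status and soft wording.** The rule says only that results are indicative, and the analyses are secondary. This limits the weight of the point but does not remove it.

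**Conclusion.** The point holds as a gap in the inference rule. As written, the rule allows a conclusion of disease modification with no early-start advantage at week 80, contrary to the picture in the Fig. 2 caption. That gap follows from the text and needs no numerical assumption.

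Its size does. For a fully reversible effect that grows with severity, the rule is met in roughly 10-55% of trials under set A and 25-89% under set B. The residual SD, slope SD, progression rate and shape of effect are all assumed, so these are illustrations and not estimates for levodopa. For constant or slow-onset effects the figure is at most about 6%.

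A reader might infer that the false-positive rate of the trial's main test is inflated. It is not. The primary comparison is powered and tested separately, "with a 0.05 two-sided significance level", and the slope rule does not enter it. The sample size is also unaffected. What is exposed is the secondary conclusion about mechanism. It should be fixed, but it does not undermine the primary analysis.

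**What to change.** In the pre-specified inference in Statistics, state that disease modification is concluded only if three conditions hold: the primary week-80 UPDRS difference favours early start with its 95% CI excluding 0, worsening is faster on placebo in phase 1, and phase 2 slope non-inferiority is shown. Amend the sentence on equal phase 2 slopes in the same section so that it carries the same condition.

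This takes one added condition and one aligned sentence. It needs no new data and no more patients, because the week-80 result is already the powered primary outcome. The price is a lower chance of making the claim when it is true: about 47-73% instead of 51-89% under a true 4-point effect, on the set B assumptions. A softer alternative is to state that the slopes are interpreted only alongside the primary result. That costs less power but leaves more to judgement.

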**Fig. 1 Fig1:**
[figure not shown]
Delayed-start design. Studies with a delayed-start design investigate two agents: active treatment (*solid line*) and controlled treatment (*dashed line*). In phase 1, patients are randomised to either active (levodopa) or controlled (placebo) treatment. In phase 2, both groups receive active treatment

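### The second slope inference rule turns an inconclusive phase 2 non-inferiority test into a finding of symptomatic effects only

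*Protocol article*

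**What the plan says.** All of this stands in the protocol article, Methods, Statistics, unless another place is named.

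- The week-80 UPDRS comparison is the main outcome. The slope comparisons are secondary and "serve only to differentiate between the different types of treatment effects (direct symptomatic vs disease modifying".
- The phase 2 analysis takes "Visit 5 (44 weeks), Visit 6 (56 weeks), Visit 7 (68 weeks), and Visit 8 (80 weeks) to test equality of progression in phase 2", by a non-inferiority test on the slope difference, "using a non-inferiority margin of 0.055 UPDRS points difference in increase per week".
- Two readings are then fixed, both conditional on faster placebo-group progression in phase 1. The favourable one: if "the non-inferiority assumption assuming equal progression is met in phase 2, this will be indicative of a true disease-modifying effect". The unfavourable one: if "non-inferiority of slopes during phase 2 is not demonstrated, then the results are indicative of only direct symptomatic effects".
- No third reading is given, and the unfavourable one does not require the slopes to be shown to differ.
- The only sample size calculation is for the week-80 difference in means, "using a two-group *t*-test with a 0.05 two-sided significance level".
- No separate significance level is given for the non-inferiority test, but "In all analyses statistical uncertainties will be expressed in 95 % confidence intervals".
- The design figure's caption explains why phase 2 carries the mechanistic argument: "In phase 2, both groups receive active treatment".

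**The concern.** Failing to show non-inferiority means only that a slope difference of 0.055 points/week or more has not been excluded. That can happen because the early-start group really loses ground in phase 2, or because the estimate is imprecise. The second rule does not separate the two. It attaches a substantive conclusion, that the phase 1 difference was purely symptomatic, to a result that may carry little information either way.

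What is at stake is the label put on the mechanism. The article gives the separation of symptomatic from disease-modifying effects as the reason for the delayed-start design, and these two rules are its only pre-specified reading of the slopes. The unfavourable rule also makes no reference to the week-80 result, so a trial with a week-80 advantage for early start could still carry the symptomatic-only label because the slope interval was wide.

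**Working it through.** **The plan's own figure.** Inputs (Statistics): difference 4, SD 13, two-sided 0.05, power 80%. Normal approximation: n = 2 × (1.960 + 0.842)² × 13² / 4² = 165.8, so 166 per arm. The exact t-test calculation gives 167 (power 0.8005). Allowing for 25% withdrawal, 167 / 0.75 = 222.7, so 223 per arm and 446 in total. The stated figures reproduce. They concern week 80 and say nothing about the precision of the slopes.

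**Inputs for the slope test.**
- Margin 0.055 points/week (Statistics). Over weeks 44 to 80 this is 0.055 × 36 = 1.98 points.
- Visits at weeks 44, 56, 68 and 80, mean 62; sum of squared deviations 18² + 6² + 6² + 18² = 720.
- One-sided 2.5%, taken from the planned 95% intervals.
- n = 167 per arm (planned evaluable number) or 223 (everyone enrolled). A random effects model can use incomplete follow-up, so the effective number may lie between.
- Total SD of a patient's phase 2 slope: **not in the article, assumed 0.15 to 0.30 points/week**. The SD of 13 is for a score at a single visit.
- The phase 1 condition is assumed not to alter the distribution of the phase 2 slope estimate.

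**Formulas, true slope difference 0.** SE = SD × √(2/n). Chance of showing non-inferiority = Φ(0.055/SE − 1.96). Chance of the symptomatic-only label = 1 minus that.

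Example, SD 0.20 and n = 167: SE = 0.20 × 0.1094 = 0.0219; 0.055/0.0219 − 1.96 = 0.55; Φ = 0.71; false label 29%.

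| Slope SD per week | False label, 167 per arm | False label, 223 per arm | Share of failures whose 95% interval includes 0 (167 per arm) |
|---|---|---|---|
| 0.15 | 8% | 3% | 70% |
| 0.20 | 29% | 17% | 91% |
| 0.25 | 48% | 36% | 95% |
| 0.30 | 61% | 51% | 96% |

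The last column is the core of the point. When slopes are truly equal, most failures are results that show no slope difference at all.

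**Where power would be adequate.** For 80% power, SE must be at most 0.055 / (1.960 + 0.842) = 0.0196. That means a slope SD of at most 0.0196 × √(167/2) = 0.179 with 167 per arm, or 0.207 with 223.

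**A second route to the slope SD.** If the SD is 13 at every visit, the between-visit correlation ρ is constant and true slopes do not vary between patients (an optimistic model), the slope SD is 13 × √(1 − ρ) / √720. For assumed ρ of 0.7, 0.8 and 0.9 this gives 0.265, 0.217 and 0.153. Power under equal slopes is then 47%, 64% and 91% at 167 per arm, and 59%, 76% and 97% at 223.

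**Sensitivity to the level.** At one-sided 5% and 167 per arm, power at SD 0.20, 0.25 and 0.30 is 81%, 64% and 51%. The problem shrinks but does not go away.

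**The case against.** The rules are limited to secondary analyses and use the cautious word 'indicative'. Demanding a positive non-inferiority result before claiming disease modification is a legitimate burden of proof, and the error runs in the conservative direction: it can withhold that claim but cannot create it. All of this stands, and it lowers the severity. It does not rescue the second rule, which goes beyond withholding a claim and asserts the opposite one.

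Three stronger readings are tempting, and the document does not support them.

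- A reader might infer that the rule overrules the primary result. It does not. The week-80 estimate, test and interval stand whatever the slopes show; only the interpretive label changes.
- A reader might infer that the non-inferiority test is known to be under-powered, or that a large share of trials would be mislabelled. Neither is established. The article gives no slope SD or correlation, and at a slope SD of 0.15 power is 92% with 167 per arm. Nor is the absence of a power calculation for a secondary test a fault in a journal article, which refers to a full protocol that is not shown here.
- A reader might infer that both arms are scheduled on the same regimen for all 40 weeks of phase 2. Table 1 puts the delayed-start group on a starting schedule in weeks 41 and 42, so the schedules match in weeks 43 to 80 only.

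**Conclusion.** The second inference rule is wrong as written, because it reads an inconclusive test as evidence for a purely symptomatic effect. The logical point needs no assumption and holds at any power below 100%. Its practical size cannot be fixed from the article. With truly equal slopes, phase 1 passed and one-sided 2.5%, the false label would occur in about 3% to 61% of trials, over assumed slope SDs of 0.15 to 0.30 points/week and 167 to 223 patients per arm. These figures are illustrations. The effect is confined to the secondary, mechanistic interpretation. Severity: should fix.

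**What to change.** Keep the phase 1 condition, and replace the two readings by three that cannot overlap, based on the 95% confidence interval of the phase 2 slope difference (early minus delayed, so that positive values mean convergence):

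- (a) Upper limit below 0.055: indicative of a disease-modifying effect, as now.
- (b) Upper limit at or above 0.055 and lower limit above 0: slopes shown to converge, consistent with symptomatic effects only, to be read together with the week-80 difference and its interval.
- (c) Upper limit at or above 0.055 and lower limit at or below 0: a disease-modifying effect has not been demonstrated, and the slope evidence is inconclusive.

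The 4-point threshold should not serve as a boundary here, because the article gives it as a criterion of clinical relevance and not of mechanism. Reporting the interval is already planned. The change should be made before unblinding.

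The cost is wording only: no patients, visits or new analyses. The downside is that some results will be called inconclusive. If the slopes truly converge at 0.055 points/week, category (b) is reached with probability Φ(0.055/SE − 1.96), which at 167 per arm is 92%, 71%, 52% and 39% for slope SDs of 0.15, 0.20, 0.25 and 0.30. In return, under truly equal slopes the symptomatic label at 167 per arm falls to 2.5% across that range.
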